## Telehealth Exercise Training in peripheral arterial disease – TEXT-PAD

[figure not shown]

**Figure 1.** A logic model of pilot RCT investigating the feasibility, acceptability and preliminary effectiveness of a 12-week multimodal telehealth behavioural intervention in low SES patients with PAD.

### **7.3. Recruitment procedures**

A comprehensive list of patients with PAD attending the Freeman Hospital is already kept. The research team will assess potential suitability and contact the participants by telephone. If the participant expresses interest in the study the PIS and consent form will be forwarded on. Hospital visits will be undertaken for formal consent (baseline) and the follow-up outcome assessments.

### **7.4. Consent**

Patients will be provided with appropriate participant information sheets designed in compliance with national guidance. They will have adequate time to consider the information, ask questions and have them answered sufficiently. Patients will be advised that participation is voluntary and that they may withdraw from the study at any time without having to provide a reason or affecting their care. Patients who are willing to participate will be asked to sign a consent form, and this process will be conducted by a trained delegated member of the research team. A copy of the signed consent form and participant information sheet will be filed in the patients' medical notes and a further copy will be given to the patient. The original signed consent form will be retained in the Investigator site file and the patients' GP will be informed of their participation in the study.

### **7.5. Randomisation**

Patients will be randomised in a 1:1 ratio to either the telehealth multimodal lifestyle intervention or standard care. The randomization will be performed in blocks of 15 patients, using an online randomisation generator ([www.randomizer.org](http://www.randomizer.org)).

## **8. INTERVENTION**

The intervention has been co-designed with Newcastle upon Tyne NHS Trust, Northumbria University, Healthworks NE and the Newcastle United Foundation. Patients in the intervention group will receive educational materials and videos outlining the main intervention components and how health behaviours impact upon their condition. The videos will be NUFC/Healthworks branded and be developed by the individuals from these organizations. Patients will also receive a NUFC foundation T-shirt. Shortly after allocation to the intervention group, patients will be contacted by a Health Trainer from Healthworks who will

conduct an initial assessment and consultation. Health trainers have various qualifications in health care e.g. nutrition degree, Level 4 rehabilitation qualification, all receive Healthworks training in motivational interviewing and intervention delivery. Patients will meet with their dedicated health trainer weekly for one hour via phone call/videoconference for 12 weeks and discuss the behaviours outlined below. Health trainers use many behaviour change techniques to promote modification of risk factors such as goal setting, problem solving and self-regulation.

### *Smoking Cessation*

Self-reported smoking habits will be assessed at baseline. Patients who smoke will receive a cessation intervention from the health trainer i.e. discussion of previous quit attempts and benefits of quitting to aid in improving health and exercise capacity. If required, nicotine replacement therapy vouchers which are redeemable at their local pharmacy will be posted to the patient. An eight-week supply of e-cigarette cartridges may also be supplied.

### *Alcohol intervention*

Health trainers will deliver a previously evaluated brief behavioural intervention to reduce alcohol intake to low-risk levels (<14 units per week) (15). Intervention materials incorporate specific techniques that target intention formation and enactment of behaviour change (e.g. information on health consequences, social support, goal setting behaviour, problem solving, restructuring the physical environment). Patients suspected to have an alcohol use disorder or risky drinking at baseline will receive additional intervention from their GP.

### *Nutrition*

Patients will receive basic nutrition education and health eating advice in line with recommendations from the British Heart Foundation and Diabetes UK. Health Trainers will provide help to overcome barriers to healthy eating.

### *Mental well-being and finances*

Patients will receive a light-touch intervention on sleep hygiene and stress management. If we discover that the patient is severely depressed, has self-harming concerns or suicidal thoughts the GP will be contacted, or patient signposted for further help. Health trainers will also help

patients to determine their eligibility to receive benefits and, facilitate access and uptake if required.

### *Supervised exercise*

The home-based exercise training will be performed twice a week for 12 weeks via Zoom (up to 5 patients per session). Each session will be comprised of warm-up (10 min), the main part (15 to 20 min), and cooldown (5 to 10 min). The training aim to develop resistance, aerobic and functional capacity such as getting up, walking, pulling, pushing, throwing, transferring body weight or external loads. An example of multimodal exercise training is shown in Box 1.

The training intensity will be progressively adjusted by increasing the load (e.g. using common household objects), increasing the complexity, speed of movements and volume of exercises by varying circuits. The intensity of the exercise will be monitored using the Borg scale (from 0 to 20) with target intensity zone from 12 to 14 (Somewhat hard to hard) (16).

In addition to the home-based training sessions, patients will be encouraged to increase their physical activity. Patients will be provided with a Fitbit device to monitor their step count and will be recommended to increase their previous week's average step count by 10%. Participants who have access to the internet will be asked to upload data to the Fitabase research platform. Data will be anonymised and will only be accessible to the research number.

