### **8.1. Usual care**

Patients randomized to the standard care group will receive general recommendations (**Box 2**) to modify risk factor and standard care as per trust guidelines given in their routine outpatient clinic appointment. Patients will also receive specific advice to perform unsupervised walking exercise for around 30 minutes three to five times a week, according to recently published NICE guidelines (8). Patients will also receive a Fitbit device so they can measure their own exercise capacity and increase as recommended. They will be asked to upload their data to the research platform if possible, as per the lifestyle intervention group.

**Box 1.** Example of exercise training module in the intervention.

| Duration     | Category                            | Exercise                                                                                                                                                                                                                                                          | Intensity (Borg Scale)     |
|--------------|-------------------------------------|-------------------------------------------------------------------------------------------------------------------------------------------------------------------------------------------------------------------------------------------------------------------|----------------------------|
| 10 min       | Warm-up                             | 
 
Active and dynamic joint mobility; coordination, balance, displacement, spatial orientation and proprioception exercises.
 
                                                                                       | Very light to fairly light |
| 15 to 20 min | Resistance                          | 
 
Resistance exercise for upper and lower limbs
 
6 to 8 exercises
 
2-3 sets of 8 to 10 repetitions
 
Interval sets 1.5-2 min
 
                                                               | Somewhat hard to hard      |
|              | Flexibility                         | 
 
Emphasis on joint mobility exercises
 
Maintenance of static positions combined with breathing techniques;
 
Proprioceptive neural facilitation techniques
 
40 sec to 1 min each exercise
 
 | Somewhat hard to hard      |

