## **10. STUDY POWER**

As per good practice recommendations for pilot studies (52), we will aim to recruit 30 patients to each arm and obtain a total sample of 60 participants. Findings of the current study will be used to inform the power calculations of future definitive RCTs.

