## **11. DATA ANALYSIS**

Primary outcome data will be reported as descriptive statistics, including rates of: patient screening, eligibility, recruitment and retention to 12-week follow-up and survey completion. Qualitative interview data will be analysed thematically to generate themes. Exploratory between-group analyses will be conducted to determine preliminary intervention effectiveness. Normality and homogeneity of variance will be performed using the Shapiro-Wilks and Levene tests, respectively. For comparison of the variables at the pre-intervention, we will perform a one-way ANOVA. To analyze the responses before and after the intervention period, two-way analysis of variance for repeated measures will be used, with the main factors being the group (and the time (pre and post intervention) with Newman-Keuls post-hoc test. The level of significance will be set at  $P < 0.05$ .

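### The between-arm ANOVA has no term for class or trainer, so it understates uncertainty if outcomes correlate within either, and it gives the later trial no design effect

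*Protocol*

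**What the plan says.** Section 7.5 randomises individuals: "Patients will be randomised in a 1:1 ratio". Section 10 sets the size: "we will aim to recruit 30 patients to each arm and obtain a total sample of 60 participants".

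Delivery is shared in one arm only. Under Supervised exercise, the intervention arm trains by Zoom two times weekly over the 12 weeks, with "up to 5 patients per session". Section 8 adds individual contact with a named person: "Patients will meet with their dedicated health trainer weekly for one hour via phone call/videoconference for 12 weeks". For controls, Section 8.1 says: "Patients will also receive specific advice to perform unsupervised walking exercise for around 30 minutes three to five times a week". It describes no class and no trainer for them.

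Section 11 names the between-arm analysis: "two-way analysis of variance for repeated measures will be used, with the main factors being the group" and time (before and after the intervention), with a Newman-Keuls post-hoc test and a significance level of 0.05. It calls these comparisons exploratory. No class or trainer term appears.

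Section 10 also says what the pilot is for: "Findings of the current study will be used to inform the power calculations of future definitive RCTs".

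**The concern.** This is a partially nested design: individual randomisation, with grouped delivery in one arm. Patients who share a class or a trainer may respond more alike than patients who do not, through the trainer's skill, the pace of the class or its group dynamics. The intervention-arm mean then varies more than 30 independent patients would imply. An ANOVA with only group and time cannot see this.

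Two things are at stake. Within the pilot, the error bars and P values on walking distance, quality of life and the other secondary outcomes may look more precise than they are. Beyond it, the pilot is meant to feed a power calculation for an intervention delivered by classes and trainers, and nothing in the stated analysis lets clustering enter that calculation. If class and trainer membership is not recorded during delivery, it may be hard to recover afterwards.

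**Working it through.** **The plan's own figure.** 2 × 30 = 60, which agrees with Section 10. No effect size, SD, power or dropout is given, so there is no power calculation to reproduce.

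**Inputs from the protocol.** n = 30 per arm, 1:1; class size m at most 5, hence 30/5 = 6 classes if full; controls ungrouped (cluster size 1); significance level 0.05, taken as two-sided.

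**Assumptions, not in the protocol.** ICC 0.01 to 0.10 for the change score; classes full and stable in membership; for trainers, hypothetical caseloads of 10 or 15.

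**Formulas.**
- Design effect in the intervention arm: DE = 1 + (m − 1) × ICC.
- Variance of the between-arm difference relative to independence: VR = (DE + 1)/2.
- True standard error (SE) over naive SE: √VR. The naive SE is therefore too small by 1 − 1/√VR.
- True type I error: 2 × [1 − Φ(1.96/√VR)].

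**Worked case, m = 5, ICC 0.10.** DE = 1 + 4 × 0.10 = 1.40; VR = 2.40/2 = 1.20; √VR = 1.095. The naive SE is 1 − 1/1.095 = 8.7% too small. Effective n in the intervention arm is 30/1.40 = 21.4.

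| Patients per cluster | ICC | DE | √VR | Type I error, formula | Type I error, simulated |
|---|---|---|---|---|---|
| 5 (class) | 0.01 | 1.04 | 1.010 | 5.2% | 5.2% |
| 5 | 0.05 | 1.20 | 1.049 | 6.2% | 6.1% |
| 5 | 0.10 | 1.40 | 1.095 | 7.4% | 7.3% |
| 10 (trainer, hypothetical) | 0.01 | 1.09 | 1.022 | 5.5% | 5.6% |
| 10 | 0.05 | 1.45 | 1.107 | 7.7% | 7.6% |
| 10 | 0.10 | 1.90 | 1.204 | 10.4% | 10.4% |
| 15 (trainer, hypothetical) | 0.01 | 1.14 | 1.034 | 5.8% | 5.7% |
| 15 | 0.05 | 1.70 | 1.162 | 9.2% | 9.5% |
| 15 | 0.10 | 2.40 | 1.304 | 13.3% | 13.4% |

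The simulation (60,000 runs, 30 per arm) used a t test on change, which equals the group-by-time test when there are two time points. At ICC 0 with m = 5 it returned 5.05%, as it should.

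**Effect on the SD.** The expected squared SD in the clustered arm is σ² × [1 − ICC × (m − 1)/(n − 1)]. For m = 5 and ICC 0.10 this is 1 − 0.10 × 4/29 = 0.9862, so the SD is 0.9931 of its true value. At ICC 0.05 it is 0.9965, and at 0.01 it is 0.9993.

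**Effect on a later trial.** With equal arms and groups of five, the total sample scales with VR: 10% larger at ICC 0.05 and 20% larger at 0.10. As an illustration, assume a standardised difference of 0.5, 80% power and two-sided 0.05. Then n per arm = (1 + DE) × (1.960 + 0.842)²/0.25.

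| ICC | n per arm needed | Power if 63 per arm is kept |
|---|---|---|
| 0 | 63 | 80% |
| 0.01 | 65 | 79% |
| 0.05 | 70 | 76% |
| 0.10 | 76 | 73% |

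**The case against.** The strongest reply is that the effect is conditional and, where the protocol gives a group size, small. The protocol states a cap on session size. It does not say that the same patients stay together, and without stable membership the formula with m = 5 does not strictly apply. It gives no ICC. With classes of five and an ICC up to 0.05, a nominal 5% test becomes at most about 6%. The higher figures depend on trainer caseloads that the available text does not give; Section 7.2 (Research staff), listed in the contents, was not in that text and may describe staffing. The tests are exploratory, no stated decision rests on them, and the primary outcomes are descriptive rates and interviews. All of this stands. It limits the severity and makes the claim conditional. It does not remove it, because a dedicated trainer is a stable link even if classes mix.

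It could also be said that random-effects structure belongs in a statistical analysis plan. That would hold if the protocol were silent, but Section 11 names the test, its factors, the post-hoc procedure and the significance level.

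A reader might infer that the SDs handed to the later trial would be wrong. They would not be, to any useful degree: the understatement is under 1% with classes of five, and Section 10 does not say that SDs are what will be carried forward. A reader might also infer that the definitive trial will be underpowered. The protocol does not say that its planners would omit a design effect. It only provides nothing from which to derive one.

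**Conclusion.** The point holds in conditional form. The protocol fixes an analysis that assumes independent patients, although delivery is shared in the intervention arm. If outcomes correlate within class or trainer, the between-arm standard errors and P values are too small.

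With stable classes of five and an assumed ICC of 0.01 to 0.10, the standard error is about 1% to 9% too small and the type I error about 5.2% to 7.3%. Hypothetical trainer caseloads of 10 to 15 would give about 5.5% to 13%. It would go too far to say that the P values are too small as a matter of fact, since that needs a positive ICC and reasonably stable groups, and the protocol establishes neither.

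The more lasting consequence is for the next trial, which would start without a design effect for an intervention delivered in groups. The pilot's primary feasibility conclusions are unaffected. This is a worthwhile, inexpensive improvement and not a threat to the study.

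**What to change.** 1. Add two fields to the data collection for each intervention patient: exercise class and health trainer. If patients move between classes, record which class they attended.
2. In Section 11, replace the repeated-measures ANOVA with a comparison of the 12-week value adjusted for the baseline value already collected, reported as a difference with a confidence interval.
3. Add a partially nested sensitivity analysis, with a class or trainer effect in the intervention arm only. Use small-sample degrees of freedom, or show the interval at fixed ICCs of 0.05 and 0.10, because about six classes cannot estimate an ICC with useful precision.
4. In Section 10, state that the definitive trial's sample size will be computed over that ICC range.

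The cost is two extra data fields, a different model and slightly wider intervals. Any ICC estimated from this pilot will be imprecise and should be reported as such. Recruitment, randomisation and delivery do not change.

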### **8.1. Usual care**

Patients randomized to the standard care group will receive general recommendations (**Box 2**) to modify risk factor and standard care as per trust guidelines given in their routine outpatient clinic appointment. Patients will also receive specific advice to perform unsupervised walking exercise for around 30 minutes three to five times a week, according to recently published NICE guidelines (8). Patients will also receive a Fitbit device so they can measure their own exercise capacity and increase as recommended. They will be asked to upload their data to the research platform if possible, as per the lifestyle intervention group.

**Box 1.** Example of exercise training module in the intervention.

| Duration     | Category                            | Exercise                                                                                                                                                                                                                                                          | Intensity (Borg Scale)     |
|--------------|-------------------------------------|-------------------------------------------------------------------------------------------------------------------------------------------------------------------------------------------------------------------------------------------------------------------|----------------------------|
| 10 min       | Warm-up                             | 
 
Active and dynamic joint mobility; coordination, balance, displacement, spatial orientation and proprioception exercises.
 
                                                                                       | Very light to fairly light |
| 15 to 20 min | Resistance                          | 
 
Resistance exercise for upper and lower limbs
 
6 to 8 exercises
 
2-3 sets of 8 to 10 repetitions
 
Interval sets 1.5-2 min
 
                                                               | Somewhat hard to hard      |
|              | Flexibility                         | 
 
Emphasis on joint mobility exercises
 
Maintenance of static positions combined with breathing techniques;
 
Proprioceptive neural facilitation techniques
 
40 sec to 1 min each exercise
 
 | Somewhat hard to hard      |
|              | Aerobic exercise (circuit training) | 
 
Global exercises, involving large muscle groups focused on aerobic capacity
 
Circuit of 3 to 4 exercises
 
Stimulus – 30 sec to 1 min
 
Passive interval (1 min)
 
                          | Somewhat hard to hard      |
| 5 to 10 min  | Cooldown                            | 
 
Active and static stretching exercises
 
Breathing relaxation exercises
 
                                                                                                                                  | Very light to fairly light |

**Box 2.** Walking intervention for patients randomised to standard care.

**Step 1:** Warm up. Stretch your calf and thigh muscles in each leg for 10 to 15 seconds.

**Step 2:** Start walking. Walk at a fast-enough pace for about 5 minutes, even though it may cause some mild pain.

**Step 3:** Stop and rest. After 5 minutes of mild or moderate pain, stop and rest until the pain goes away.

**Step 4:** Repeat the walk-and-stop routine several times. During the first two months of your walking program, build up slowly to walking a total of 35 minutes each session, not counting the rest breaks. Keep adding a few minutes until you're at the goal of walking 50 minutes.

**Step 5:** Cool down. Finish by walking slowly for 5 minutes. Then, stretch your calf and thigh muscles again.

**Step 6:** Stick with it.

## **9. OUTCOME MEASUREMENTS**

### **9.1. Primary outcomes**

Feasibility will be determined by calculating the rate of patient screening, eligibility, recruitment, retention at 12 weeks and adherence to the intervention (number of sessions attended and completed).

Patient acceptability of the intervention and study experience more broadly will be determined through semi-structured qualitative 1-2-1 interviews and/or focus groups. Given the challenges of conducting focus groups remotely, and anticipated characteristics of the participant group, we expect that 1-2-1 interviews will be more practical and facilitative. We will purposively sample participants from both study arms so that the experiences of patients from varied ethnic backgrounds, age and gender are represented. Acceptability of the intervention will be guided by Sekhon et al.'s Theoretical Framework of Acceptability (17) and the NIH Behavior Change Consortium's Best Practices and Recommendations. We will also ask patients about their experience of participating in the study e.g. informed consent process, time commitment, acceptability of measures e.g. readability, burden etc. We will also ask for their experiences, thoughts and attitudes towards current usual care for PAD. Interviews will be conducted until data saturation is reached in a maximum of 20 participants.

All focus groups will be audio recorded and transcribed, and these data will be analysed thematically to generate themes and outcomes. Participants will receive a £20 voucher as reimbursement for their participation.

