### **6.2. Primary objectives**

To determine:

- Rates of patient screening, eligibility, recruitment, and retention to 12-week follow-up
- Patient compliance to the intervention (number of sessions attended and completed)
- Patient acceptability of the intervention through semi-structured qualitative interviews

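### The interview sample for the acceptability outcome is not chosen on session attendance or withdrawal, so it can meet the stated frame with few or none of the patients who stopped

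*Protocol*

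**What the plan says.** Section 6.2 lists among the primary objectives "Patient acceptability of the intervention through semi-structured qualitative interviews", and Section 9.1 repeats acceptability as a primary outcome. The sampling rule in Section 9.1 is purposive and draws on both arms so that "the experiences of patients from varied ethnic backgrounds, age and gender are represented". The stopping rule is: "Interviews will be conducted until data saturation is reached in a maximum of 20 participants". The interviews cover the intervention, the experience of taking part in the study, and views on current usual care.

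Sections 6.2 and 9.1 also make retention to 12 weeks and the number of sessions attended and completed part of primary feasibility. Section 10 sets the size: "we will aim to recruit 30 patients to each arm and obtain a total sample of 60 participants". Section 7.4 tells patients that "they may withdraw from the study at any time without having to provide a reason or affecting their care".

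The protocol does not use attendance, adherence or withdrawal to choose interviewees. It also makes no provision for approaching a patient who has stopped.

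**The concern.** The primary research question in Section 5 asks in part whether the intervention is acceptable to patients. Not attending, or leaving, is the plainest behavioural sign that it did not suit someone. The programme is demanding: two exercise sessions a week for 12 weeks (24) plus a weekly trainer meeting (12) make 36 contacts, so attendance can vary widely. The target group is also one that Section 4 links with difficulty in engaging.

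The frame secures variety in who the patients are, but not in how far they took part. Two samples could both comply, one made up wholly of regular attenders and one including several who stopped, and they might give different pictures of acceptability. At stake are the reasons for stopping, which a definitive trial would need in order to change the programme, and some selection towards favourable accounts.

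This is not a detail normally left to an analysis plan, because the protocol itself fixes the sampling characteristics.

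**Working it through.** **No figure to reproduce.** The total of 60 is a good-practice target, and the protocol gives no expected withdrawal or retention rate. The check is a reading of the frame followed by illustrations.

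**Inputs from the protocol.** Sample of 60, with 30 per arm (Section 10); at most 20 interviewees from both arms (Section 9.1).

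**Assumptions.** Ten interviews fall in the intervention arm; withdrawal in that arm is 3 or 6 of 30; where stated, willingness to be interviewed differs between those who completed and those who did not.

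**Step 1: can engaged patients fill the sample?** 20/60 = 33%. At any retention of about one third or more there are at least 20 completers. At assumed retention of 70%, 80% and 90% there would be 42, 48 and 54. Provided the completers themselves vary in ethnicity, age and gender, they can fill every place within the frame.

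**Step 2: chance of no withdrawn patient.** With k of 30 intervention patients withdrawn and 10 drawn at random, all reachable and equally willing:

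P(none) = C(30−k, 10) / C(30, 10)

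- k = 3 (10%): (20·19·18)/(30·29·28) = 6,840/24,360 = 0.281. Expected number interviewed: 10·3/30 = 1.
- k = 6 (20%): (20·19·18·17·16·15)/(30·29·28·27·26·25) = 27,907,200/427,518,000 = 0.065. Expected number: 10·6/30 = 2.

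For at most one, add the term k·C(30−k, 9)/C(30, 10). This gives 0.749 for k = 3 and 0.326 for k = 6.

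**Step 3: counting low attenders as well.** If 9 of 30 were either withdrawn or low attenders, the same formulas give 0.012 for none and 0.100 for at most one. A wider definition of disengagement therefore shrinks the problem under random selection.

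**Step 4: unequal willingness.** Let r be retention, and suppose 80% of completers but 20% of non-completers agree. The expected number of non-completers among 20 interviewees from both arms is

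20 · 0.2(1−r) / [0.8r + 0.2(1−r)]

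| Retention (assumed) | Equal willingness | 80% versus 20% |
|---|---|---|
| 70% | 6 | 20·0.06/0.62 = 1.9 |
| 80% | 4 | 20·0.04/0.68 = 1.2 |
| 90% | 2 | 20·0.02/0.74 = 0.5 |

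Purposive selection is not a random draw, so Steps 2 to 4 show orders of size and do not predict what will happen.

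**The case against.** The strongest reply is that silence is being read as exclusion. Section 9.1 does not call the three features the only criteria, does not restrict interviews to completers, and does not tie them to the follow-up visit. Study arm is part of the frame too. Demographic variety selects against no one and suits a trial in deprived patients. The interviews ask about time commitment and burden, so regular attenders can voice criticism. Retention and attendance are reported in any case, so poor uptake would be visible whoever is interviewed. All of this stands, and it limits the point to a missing sampling characteristic and to reasons that may be lost.

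A reader might go further and infer that saturation among attenders will close sampling before any negative experience is heard. The protocol does not support that. It does not say attenders are interviewed first, and the timing of interviews cannot be read from the Gantt chart as reproduced. A reader might also infer that a withdrawn patient is certain to be missed. That would follow only if interviews were limited to those attending follow-up, a condition stated nowhere; and a patient who skipped sessions may still attend follow-up.

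What the reply does not remove is that nothing in the stated rule ensures that those who stopped are sought. Sampling by arm does not do so, since arm is neither attendance nor retention.

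**Conclusion.** The point holds as a design improvement; it is not a contradiction or a false statement in the protocol. The frame for a primary outcome omits the characteristic closest to the question, although the trial records it, and a compliant sample can contain few or none of those who stopped.

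The size is moderate and depends on assumptions. On a like-for-like measure, the chance of no withdrawn interviewee in the intervention arm is 28% at 10% withdrawal and 6.5% at 20%, given 10 interviews in that arm and random selection with equal willingness. If those who stopped are less willing to talk, the risk is greater; if low attenders are counted as well, it is smaller under random selection. The protocol fixes none of these rates.

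It might also seem to follow that most of the 20 places should move to the intervention arm. That is a trade-off and not a correction, because Section 5 asks about the study as well as the intervention, and the interviews also explore usual care.

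**What to change.** Keep the cap of 20, both arms and the three demographic features. In Section 9.1:

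- Add attendance band and withdrawal status as purposive sampling characteristics for the intervention arm, with the bands defined in advance.
- State a minimum number of low attenders or withdrawn patients who agree to interview, to be sought before saturation is declared. The team should choose the number. It is a target for effort, since patients may decline.
- Allow the invitation when a patient stops, as well as at the end. The consent wording should make clear that interview is optional and that leaving still needs no explanation.

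The cap on interviews and vouchers is unchanged, and the data needed are already collected. The costs are some extra outreach and possibly a small change to the participant information. That change is best settled before recruitment, because a later one would miss early leavers.
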